# Physiological and Psychological Effects of Parent-Delivered Traditional Thai Massage in Children With Autism: Protocol for a Randomized Controlled Trial

**DOI:** 10.2196/41839

**Published:** 2023-02-08

**Keywords:** autism, massage, randomized controlled trial, protocol

## Abstract

**Background:**

Although many autistic children receive massage as a complementary therapy, it is not included in evidence-based practice for autism because evidence of its efficacy is lacking. Further, prior studies have failed to identify objective indicators of core symptoms or elucidate their mechanisms.

**Objective:**

We developed a parent-delivered traditional Thai massage (TTM) intervention for children with autism, aiming to experimentally determine whether children with autism truly experience positive effects from parent-delivered TTM and determine possible mechanisms of the observed effects.

**Methods:**

A 2-armed, parallel randomized controlled trial was conducted between February 2022 and June 2022. Forty-eight children with autism (aged 7-12 years) were recruited from the Hainan Special Education School and randomly assigned to either a parental TTM or control group at a ratio of 1:1 based on random numbers generated with Online Research Randomizer. The generated sequences were concealed in an opaque envelope. Individuals in the parental TTM group received 16 parent-delivered TTM sessions over 8 weeks at the school’s health room after school, and the control group maintained a normal daily routine. Outcomes were assessed on admission, after 8 weeks, and at a 2-month follow-up and included the effect of massage treatment on autism symptoms, measured with the Autism Treatment Evaluation Checklist score (evaluated by parents and a blinded teacher), physiological parameters (ie, heart rate variability and gait), and the Parenting Stress Index, Fourth Edition–Short Form.

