Furthermore, the refractory and lifelong nature of autism has profound implications for parents of autistic children and evidence shows that parents of children with autism experience more parenting stress than parents of nonautistic children or children diagnosed with other disabilities [55,56]. One recent review suggested that family-based interventions for mental disorders in children are becoming increasingly important, with more positive outcomes when parents are involved in the treatment [57]. Previous research revealed that parents who engaged in a massage-based intervention not only satisfied family-based care needs [58] but also showed relieved anxiety [42] and strengthened parent-child bonding [37,38,59]. The effects of TTM delivered by the parents of autistic children on these outcome measures have not been verified. This study aims to assess the effects of parental-delivered TTM in children with autism by evaluating changes in symptoms and physiological parameters (ie, gait and HRV). The primary objective of the study is to assess the effectiveness of parental TTM in improving symptoms of autism according to the Autism Treatment Evaluation Checklist (ATEC). Secondary objectives are to evaluate instant and cumulative effects of the parental TTM intervention via an assessment of gait and HRV and explore the relationship between symptom improvement and observed changes in physiological parameters. The tertiary objective is to examine changes in levels of parental stress after parents have administered the TTM intervention. The following four research questions will be addressed: (1) Do core symptoms significantly improve (ie, does ATEC score improve) in autistic children after parental TTM in comparison with the control group? (2) Do HRV and gait indicators significantly improve in children with autism after parental TTM? (3) Is ATEC score improvement related to observed changes in physiological parameters? (4) How does parental stress change throughout the intervention period, as measured by the Parenting Stress Index, Fourth Edition–Short Form (PSI-4-SF)?

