### Ethical Considerations

This study complies with the ethical standards of the relevant national and institutional guidelines on human experimentation and was approved by the Khon Kaen University Ethics Committee for Human Research (HE642167). The study followed the Helsinki Declaration. Results will be published in a peer-reviewed journal and presented at domestic and international academic conferences to further promote communication. This protocol was registered with the Chinese Clinical Trial Registry (ChiCTR2100051355).

Researchers provided parents with information about the study and obtained informed consent from them while their children were in school. The parent or guardian signed the document and returned it to the school researcher or the teacher. Before the study, the parents were responsible for asking their children about their willingness to participate in the study. Children whose parents provided informed consent took part in the study. The researchers explained the study methods verbally to the children and parents and demonstrated the tests that would be performed on the children; the teachers and parents observed each child’s reaction to determine if the child consented or not before the test.

In the massage group, the participants were paid US $7 for each TTM session. In the control group, each volunteer participated in the evaluation 4 times and was paid US $7 each time. The decision was made that after data collection was finished, if good results were obtained in the parental TTM group, the control group would also be given training in TTM. Each teacher volunteer who participated in the 3 stages of assessment received US $30 for each stage.

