#### TTM Training

The parents of autistic children who were enrolled in the study took part in 3 TTM training sessions. Each 3-hour session was hosted by experts at the health room of Hainan Special Education School. Parents of participants in the intervention group were trained in TTM by an experienced traditional Thai masseur with a massage qualification until they became able to perform the experimental intervention. Thereafter, the massage trainer monitored the parents to ensure that they continued to perform TTM properly at each session.

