### Secondary Outcome Assessments

#### Gait

Gait was measured using a wearable BTS G-Walk device (BTS Bioengineering Company). Experimental gait data were collected at a frequency of 100 Hz and transmitted to a computer via a Bluetooth connection. All gait parameter measurements have been determined to have high test-retest and intertrial reliability (intraclass correlation coefficient: 0.728-0.969 and 0.84-0.99, respectively) [66,67]. Wireless internet was required for the gait tests, which were carried out on a flat surface that measured at least 10 × 10 m. Prior to performing the test, the height of the participant was entered, and an adjustable elastic band was placed around the participant’s waist. When taking the test, participants stood in place for a few seconds. After confirming that the sensor was connected to the computer via Bluetooth and the connection was stable, each child volunteer followed a marked 7-m path back and forth while walking normally. Teachers or parents were allowed to provide verbal cues but not physical assistance.

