#### HRV Measurement

UBiomacpa (version 1; Biosense Creative) was used to detect the activity of the autonomic nervous system. The HRV test was carried out in an independent, quiet room at an ambient temperature of 26 °C. Before starting the test, the tester ensured that the equipment was properly connected. After receiving TTM, the autistic children were placed in a sitting position with a pulse sensor attached to their left index finger, and they underwent an HRV test for 2 minutes that was administered by a physiotherapist. When the test was complete, the device automatically generated a data report via a connected computer.

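### The three stated assessment occasions conflict with the controls' four evaluations and leave no basis for estimating the instant effect on gait and HRV

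*Protocol article*

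**What the plan says.** - **Schedule (Abstract, Methods).** "Outcomes were assessed on admission, after 8 weeks, and at a 2-month follow-up". The same sentence names among the outcomes "physiological parameters (ie, heart rate variability and gait", so the three occasions apply to both physiological measures.
- **Objective (end of Prior Work).** "Secondary objectives are to evaluate instant and cumulative effects of the parental TTM intervention via an assessment of gait and HRV".
- **Number of evaluations (Ethical Considerations).** "In the control group, each volunteer participated in the evaluation 4 times and was paid US $7 each time". For teachers: "Each teacher volunteer who participated in the 3 stages of assessment received US $30 for each stage". The massage arm is paid per session, and no evaluation count is given for it.
- **Measurement.** For HRV: "After receiving TTM, the autistic children were placed in a sitting position with a pulse sensor attached to their left index finger". The Gait section describes the walk ("each child volunteer followed a marked 7-m path back and forth while walking normally") but not when it took place relative to a session.
- **Analysis (Data Collection, Management, and Analysis).** Holm correction is planned for comparing immediate, short-term and long-term effects. HRV and gait changes are to be tested within each group by paired t or signed-rank tests.
- **Results.** Three time points are named for the ATEC: immediate, short term and long term. Admission is not among them.

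**The concern.** An instant effect is a change across one session. It needs a reading shortly before the session, a reading shortly after it and, for a randomised comparison, the same two readings in controls. The stated schedule provides none of these, yet the effect is a declared secondary objective and is put into a multiplicity-corrected comparison.

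Analysis had not begun when the article was written. If the occasions stay undefined, the baseline for the instant effect will be chosen with the data in hand. A post-session value set against admission, or tested within the massage arm only, could then be reported as an instant effect of massage when it may also carry whatever else changed between the two readings.

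**Working it through.** The check is a count and a match of occasions. No sample-size or power figure enters it.

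**Inputs**

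| Source in the article | What it gives |
|---|---|
| Abstract, Methods | 3 occasions, covering gait and HRV |
| Ethical Considerations | 4 evaluations per control child; 3 stages per teacher |
| Intervention | 2 sessions a week for 8 weeks |
| Data Collection, Management, and Analysis | 3 effects to compare: immediate, short term, long term |
| Results | the same 3 labels, attached to the ATEC, without admission |

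**Step 1: number of occasions.** Controls have 4 evaluations and the schedule has 3 occasions. 4 − 3 = 1 evaluation without a stated place. The teachers' 3 stages do agree with the schedule.

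**Step 2: contrasts available.** Three occasions give 3 × 2 / 2 = 3 pairwise contrasts.
- Admission to 8 weeks: 2 × 8 = 16 sessions lie between. This is a cumulative effect.
- Admission to 2-month follow-up: the same 16 sessions plus the follow-up period.
- 8 weeks to 2-month follow-up: no scheduled session lies between. This is persistence.

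Contrasts that bracket one session: 0 of 3.

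**Step 3: labels against visits.** Three separate effects (immediate, short term, long term) need three post-baseline readings plus a baseline: 3 + 1 = 4 occasions. The stated schedule has 3 − 1 = 2 post-baseline readings, one too few. Adding one immediate occasion gives 3 + 1 = 4, which equals the control count. That is a plausible reconstruction, but no text shown defines the fourth evaluation. Nor does it fit the teacher-rated ATEC: 3 teacher stages cannot hold a baseline and all three labelled times, although the Results section names those times for the ATEC.

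**Step 4: measurement sections.** Read as straight after a session, the HRV sentence cannot describe admission in the massage arm, when no massage has yet been given, and cannot describe controls at any visit. It could fit the 8-week visit or an unlisted one. If it describes the 8-week visit, the instant and cumulative effects are mixed there. No pre-session HRV reading is described, and the Gait section gives no timing at all.

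**Step 5: the planned test.** A paired test needs a defined first value. For the immediate effect the article names none, so the contrast is not specified for either arm.

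**The case against.** The strongest reply is that the visit detail sits elsewhere. Figure 1 and the SPIRIT appendix are not shown, and a journal article condenses the full protocol. The visible text even suggests that an immediate assessment took place: four control evaluations, HRV after massage, and an immediate effect in the analysis. This stands as a limit. A reader might infer that the readings were never taken; the documents do not show that. It does not remove the point, because the article prints a schedule that disagrees with its own evaluation count and objective.

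A second reply is that the second research question asks only whether HRV and gait improve after massage, without naming controls, so within-group tests suffice. This stands only in part. Even a within-group test needs a defined before reading, and a change within the massage arm alone cannot be attributed to massage.

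Three stronger readings are tempting and are not supported:
- A reader might infer that several days of parent training separated the admission reading from the first session. The TTM Training section does not date the training, the admission tests or the first session.
- A reader might try to size the problem from the reliability ranges in the Gait section. The article does not say which coefficients are same-day or between-day. The ranges come from two sources, and their ends need not belong to the same gait parameter.
- A reader might conclude that controls had no comparable condition at their fourth evaluation. What they did then is unstated, which is not the same as shown to be absent.

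**Conclusion.** The point holds as an internal contradiction with a consequence for one secondary objective. The article states 3 occasions and 4 control evaluations. None of the 3 contrasts available from the stated schedule estimates an instant effect on gait or HRV, and the immediate time point in the Results section cannot be matched to the Abstract. The conclusion applies to the schedule as printed and assumes that the Abstract's list is meant to be complete for gait and HRV. No bias or loss of precision can be put into figures from the documents. The cumulative contrast for gait and HRV and the ATEC comparison at 8 weeks and at follow-up can still be made from the stated visits, provided that the timing of the 8-week HRV reading relative to a session is made clear. Since analysis had not started, the matter can be settled from the visit records before any result is known.

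**What to change.** Before analysis:

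1. Make the Abstract, Ethical Considerations, HRV Measurement, analysis and Results sections list the same occasions, and say which of them immediate, short term and long term denote, for which outcomes.
2. State for each arm when gait and HRV were taken relative to a session, and what the controls' fourth evaluation was.
3. If same-day before and after readings exist in both arms, define the instant effect as the between-arm difference in that same-day change, with a confidence interval, and do not rely on within-group paired tests alone.
4. If only admission and post-session readings exist, withdraw the instant-effect claim and report those readings descriptively, noting that controls followed their usual routine.

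No visit can be added, because data collection ended on June 20, 2022. A new resting condition for controls would in any case be a different comparator from the one the trial used.

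The cost is a check of the visit records and edits to a few sentences. The downside is that one secondary claim may be downgraded.

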**Results:**

We finished all data collection on June 20, 2022. Data analysis will be started, and we expect to publish results in 2023.

**Conclusions:**

This study will provide further evidence for massage treatment of autism and provide support for family-based care.

**Trial Registration:**

Chinese Clinical Trial Registry ChiCTR2100051355; https://tinyurl.com/3dwjxsw5

**International Registered Report Identifier (IRRID):**

DERR1-10.2196/41839

## Introduction

### Background

Autism is a neurodevelopmental disorder that affects central nervous system development. The core symptoms are characterized by social interaction and social communication deficits and restrictive-repetitive behavior patterns [1]. The disorder is not associated with any particular culture, ethnicity, race, or socioeconomic group [2]. The majority of individuals with autism also have motor disorders, sensory disorders, anxiety, hyperactivity, sleep disorders, or autonomic nervous system (ANS)-associated disorders [3-5]. The prevalence of autism has risen rapidly in the last decade. An assessment commissioned by the World Health Organization in 2012 estimated the global prevalence of autism to be approximately 1% [6]. An updated report from the US Centers for Disease Control and Prevention showed that 1 in 44 children aged 8 years was estimated to have autism spectrum disorder (ASD) [7]. A survey found that the incidence of autism among children in China was comparable to that in Western countries [8].

A variety of motor disorders are common in autism [9]. Postural [10] and gait abnormalities [11,12] can appear as early as infancy [13] and persist into childhood [14,15] and adulthood [16]. Previous studies showed that motor impairment may result in atypical movement [17] and limit social interaction [18] due to sensory integration impairment [16]. This could, in turn, lead to the development of core autistic symptoms [18,19] and reduced quality of life [20].

The core symptoms of autism can be explained in part by ANS dysregulation [3,21,22]. Messina et al [23] found sympathetic activity, such as heart rate variability (HRV; the variation in time between each heartbeat), which is controlled by the ANS, may be considered an important tool for autism assessment. Measurements of HRV are considered to be the standard noninvasive method for assessing ANS function [23] and have also been suggested to be a valuable situation-specific marker of the effective regulation of children’s binary social interactions [24]. Previous reports showed that tonic HRV was significantly reduced in children with ASD compared with typically developing children [22,25]. Lory et al [25] suggested that ANS disorders in autism may lead to atypical attentional responses to sensory stimuli.

Atypical sensory responses (hyper- or hyporeactivity to sensory stimuli) are present in 90% of children with autism [26] and have been listed in the core diagnostic criteria for autism in the Diagnostic and Statistical Manual of Mental Disorders, 5th Edition, with abnormal tactile responses commonly reported [27]. Thye et al [19] reviewed the evidence of a relationship between sensory and social behavior in autism, especially in terms of touch and tactile processing irregularities, and concluded that it may be associated with social dysfunction.

### Prior Work

Massage is a touch-based therapy [28] defined as the use of the hands, feet, arms, or elbows to touch or manipulate the body surface of the person being massaged for healing and maintenance purposes [29]. Massage originates from human instinct and was developed as a kind of technology by the ancients. Historical records of massage therapy date back 3000 years, and massage therapy is mentioned in the earliest medical book in China, the *Huangdi Neijing* (*The Yellow Emperor’s Classic of Internal Medicine*), which recorded the theory of Chinese medicine and massage theory. The value of massage as a form of therapy has been recognized throughout history by ancient civilizations in China, India, Japan, Thailand, and, later, the ancient Egyptians, as well as the Greeks and Romans [30]. Since then, massage therapy has been continuously developed and applied, and is widely used in clinical practice to relieve pain, eliminate fatigue, and promote rehabilitation. A review by Field [31] outlined the clinical implementation of massage theory in recent years. Massage has recently been employed as a complementary therapy in the treatment of autism. It has been reported that 11% to 16% of people with autism receive massage therapy [32]. Initial studies in this area of research suggest that massage might have positive impacts on social communication [33,34], stereotypic behavior [35,36], sensory profiles [37,38], and language ability [39,40] in autism. According to research findings, positive touch stimuli can increase oxytocin release [41,42]. Oxytocin is known to be involved in ANS circuit regulation [41], which affects both emotional and social processes [43]. Suitable pressure stimulation is the critical feature of massage, and stimulation of pressure receptors has been shown to result in increased vagal activity. Increased vagal activity is associated with slower heart rate and enhanced attentiveness [31].

Traditional Thai massage (TTM) is believed to have ancient origins and has 3 distinctive features: deep pressure massage, work on meridian (energy) lines, and stretching of the affected muscles and joints. TTM is widely used in health care [44,45] and rehabilitation [46,47]. The results of studies conducted to date suggest that TTM may facilitate immediate and short-term improvement in HRV [48,49] and some gait parameters in nonautistic patients [50,51]. Since an increase in HRV reflects a state of relaxation due to parasympathetic activity induced by TTM, patients either with or without autism can relax and reduce their restrictive-repetitive behavior patterns. Consequently, they should improve their gait pattern and speed. TTM has also been effectively used in the rehabilitation of children with disabilities by the Bangkok Foundation for Children with Disabilities [52]. However, we only found one study [53] that reported the effects of TTM administered by masseurs on autistic behavior, and its methodology and conclusions were questionable [54]. It appears that more research is needed to explore the effects of TTM on autism by using both subjective and objective evaluation.

Furthermore, the refractory and lifelong nature of autism has profound implications for parents of autistic children and evidence shows that parents of children with autism experience more parenting stress than parents of nonautistic children or children diagnosed with other disabilities [55,56]. One recent review suggested that family-based interventions for mental disorders in children are becoming increasingly important, with more positive outcomes when parents are involved in the treatment [57]. Previous research revealed that parents who engaged in a massage-based intervention not only satisfied family-based care needs [58] but also showed relieved anxiety [42] and strengthened parent-child bonding [37,38,59]. The effects of TTM delivered by the parents of autistic children on these outcome measures have not been verified. This study aims to assess the effects of parental-delivered TTM in children with autism by evaluating changes in symptoms and physiological parameters (ie, gait and HRV). The primary objective of the study is to assess the effectiveness of parental TTM in improving symptoms of autism according to the Autism Treatment Evaluation Checklist (ATEC). Secondary objectives are to evaluate instant and cumulative effects of the parental TTM intervention via an assessment of gait and HRV and explore the relationship between symptom improvement and observed changes in physiological parameters. The tertiary objective is to examine changes in levels of parental stress after parents have administered the TTM intervention. The following four research questions will be addressed: (1) Do core symptoms significantly improve (ie, does ATEC score improve) in autistic children after parental TTM in comparison with the control group? (2) Do HRV and gait indicators significantly improve in children with autism after parental TTM? (3) Is ATEC score improvement related to observed changes in physiological parameters? (4) How does parental stress change throughout the intervention period, as measured by the Parenting Stress Index, Fourth Edition–Short Form (PSI-4-SF)?

